
## Interventions

3

### Experimental intervention

3.1

The experimental intervention will consist of techniques derived from the classical Falloon psychoeducational intervention and from the adaptations by CBT approach, both adapted for the treatment of adolescents and young adults affected by emotional and/or affective disorders in an acute psychiatric setting. The experimental intervention will be administered in a daily group context of 1-1.5 hours each within the acute psychiatric settings (during the hospitalization phase). The adoption of a daily psychoeducational intervention during hospitalization was motivated by the need to deliver a comprehensive intervention within the limited timeframe preceding discharge, considering the low length of stay in our ward. If the patient is discharged before the end of the procedure, patients can conclude the procedure in person or via teleconference. The experimental intervention will consist of the following phases: 1) engagement of the patient; 2) individual assessment; 3) informative sessions provided within the group context; 4) communication skills sessions provided within the group context; 5) problem-solving skills sessions provided within the group context; 6) social skills sessions provided within the group context. The informative sessions will deal with the following thematic modulus: 1) Primary and secondary emotions; 2) Anxiety and Sadness; 3) Unusual experiences; 4) Drugs and addictions; 5) Sleep and Biological Rhythms; 6) Medications (**Table 1**).

**Table 1 T1:** Characteristics of each module of the experimental intervention.

Module	Description
Primary and secondary emotions [figure not shown]	It provides information on Ekman’s five primary emotions, contextualizing them through facial expressions and teaching their recognition, including emotions’ body experiences. Patients also will learn the ABC model (16, 17) for managing unpleasant emotions and related thoughts.
Anxiety and Sadness [figure not shown]	It focuses on the differences between normal and pathological forms of these emotions, identifying triggering situations and body experience of anxiety and sadness. It will also teach behaviors that can reduce vulnerability to anxiety, along with strategies to manage both emotions effectively.
Unusual experiences [figure not shown]	It provides information regarding the manifestation of different “unusual experiences” that patients may develop like dissociation, derealization, depersonalization or hallucinations.
Drugs and addictions [figure not shown]	It aims to raise awareness about substances and their associated risks, offering alternative coping strategies to substance use and addressing possible behavioral addictions, particularly digital ones.
Sleep and Biological Rhythms [figure not shown]	It provides information about sleep mechanisms, proper sleep hygiene, factors influencing sleep quality (both positively and negatively), and strategies to improve rest.
Medications [figure not shown]	Available pharmacological and non-pharmacological treatments for mental disorders, indications, side effects and strategies to cope with them, treatment duration, risk factors for relapse, and effects related to abrupt discontinuation of the therapy.

All images were generated using AI.

The sessions will take place each day for a total of 12 sessions for a period of around 2 weeks. Between sessions, participants will be invited to fill out dedicated practical exercises (“homeworks”). Each session will be organized into three phases: a) the first phase will be dedicated to clarifications and questions regarding the topics previously discussed; b) the second phase will focus on the main topics of the session; and, c) in the final phase, the key points addressed during the session, will be summarized with the assignment of target homeworks to all group members. A dedicated training material will be provided to all staff members in order to guarantee the fidelity of administration of all sessions of the experimental intervention, after providing a formal training by an experienced trained clinician (**Supplementary Material 1**). At the end of each session, all participants will complete a satisfaction questionnaire in order to improve and adapt the intervention based on participants’ feedback. **Supplementary Material 2** shows the satisfaction questionnaire that has been specifically developed. At the end of each session, participants will receive informative leaflets and cards summarizing the key-points addressed during the session (**Supplementary Material 3**).

### Measurements, assessment time-points and tools

3.2

Before the administration of the study, during the first three months of the study the following tasks have been planned: a) the formal achievement of EC approval; b) the training of mental health professionals in the experimental interventions and in the use of assessment tools; c) organizing the implementation of the interventions. The recruitment of participants will take place between month 4 and month 12. The participants will be randomly assigned by the principal investigator (P.I.) only after the receipt of written informed consent by their parents (if aged less than 18 years old). Assessment will be performed between month 4 and month 24. **Figure 1** illustrates the timeline of the study.

**Figure 1 f1:**
[figure not shown]
Timeline of the study.

At the baseline will be collected socio-demographic (e.g., sex, age, educational level, occupational and living condition) and clinical characteristics (e.g., age of onset, illness duration, number of affective and/or emotional episodes and previous hospitalizations, age at first hospitalization, comorbid physical and/or mental disorder, family psychiatry history, suicidality, drug and/or alcohol use current and/or previous, current and/or previous pharmacological and/or psychosocial and/or psychotherapy interventions) of all eligible participants through validated assessment tools. Researchers who administer assessment tools, will be blinded to patient allocation. All patients will be assessed at the following time points: a) at T0 (baseline), at least 1 day before the start of the intervention; b) at T1 (post-intervention); c) at T2 (follow-up at 1 months after completion of intervention); d) at T3 (follow-up at 3 months after completion of intervention); and, e) at T4 (follow-up at 6 months after completion of intervention); f) at T5 (follow-up at 12 months after completion of intervention). During the assessment, whereas the participant feels distressed or exhausted, the assessment will be postponed in another moment in a range of 2–3 days.

At baseline, participants will be administered the following assessment tools: Difficulties in Emotion Regulation Scale (DERS) (18), Brief Psychiatric Rating Scale (BPRS) (19), Clinical Global Impression Scale - Severity (CGI-S) (20), Coping Orientation to Problems Experienced-New Italian Version (COPE-NVI) (21), Global Assessment of Functioning (GAF) (22), Internalized Stigma of Mental Illness Inventory (ISMI) (23), Mental Health Knowledge Schedule (MAKS) (24) and the Montreal Cognitive Assessment (MoCA) (25) (**Tables 2**, **3**).

**Table 2 T2:** Timeline of the assessment administration.

Assessment	T0	T1	T2	T3	T4	T5
DERS	X	X	X	X	X	X
BPRS	X	X	X	X	X	X
CGI-S	X	X	X	X	X	X
CGI-I		X	X	X	X	X
COPE-NVI	X	X	X	X	X	X
GAF	X	X	X	X	X	X
ISMI	X	X	X	X	X	X
MASK	X	X	X	X	X	X
MOCA	X					

T0, baseline; T1, end of the intervention; T2, 1 month after the end of the intervention; T3, 3 month after the end of the intervention; T4, 6 month after the end of the intervention; T5, 12 month after the end of the intervention; DERS, Difficulties in Emotion Regulation Scale; BPRS, Brief Psychiatric Rating Scale; CGI-S, Clinical Global Impression Scale - Severity; CGI-I, Clinical Global Impression Scale - Improvement; COPE-NVI, Coping Orientation to Problems Experienced-New Italian Version, GAF, Global Assessment of Functioning; ISMI, Internalized Stigma of Mental Illness Inventory; MAKS, Mental Health Knowledge Schedule; MOCA, Montreal Cognitive Assessment (MoCA).

**Table 3 T3:** Characteristics of the assessment used in the study.

Assessment	Description
DERS (18)	The DERS is a widely used scale for assessing difficulties in emotion regulation. It consists of 36 self-report items on a 5-point Likert scale, with responses ranging from 1 to 5, from “almost never” to “almost always”. Total scores range from 36 to 180, with higher scores indicating greater problems with emotion regulation. The Italian version identifies the following subscales: non-acceptance of emotional responses, difficulty engaging in distracting behaviours, difficulty controlling impulses, lack of emotional awareness, limited access to emotion regulation strategies, lack of emotional clarity. This scale will be used to assess the impact of the intervention on emotion regulation skills.
BPRS (19)	The BPRS is the most widely used inventory of psychiatric symptoms for assessing disease severity, particularly for evaluating outcomes in psychopharmacological and psychosocial clinical trials. The test consists of a semi-structured interview with 24 items, with a severity score of 7 points, completed by the interviewer. Scores below 30 indicate mild symptoms, while scores between 31 and 41 indicate moderate symptoms and scores above 42 indicate severe symptoms. This scale will be used to assess whether the intervention has an effect in reducing the severity of symptoms.
CGI-S and CGI-I (20)	The CGI has two components: the CGI-S, which rates illness severity, and the CGI-I, which rates change from the initiation (baseline) of treatment. The CGI-S is a scale that assesses the severity of illness by asking the evaluator a question: ‘Based on your experience with this type of patient, how ill, from a psychological point of view, is the patient at this time?’ The degree of illness consists of seven levels: 1 = normal, not ill at all; 2 = only marginally ill; 3 = mildly ill; 4 = moderately ill; 5 = significantly ill; 6 = severely ill; 7 = among the most severely ill patients. This assessment is based on symptoms, behaviour and functioning observed and reported over the last seven days. It is clear that symptoms and behaviour can fluctuate over the course of a week; the score should reflect the average level of severity over the seven days. The CGI-I is similarly simple in its format. Each time the patient is visited after a treatment initialization, the clinician compares the patient’s overall clinical condition to the one-week period just prior to the initiation of the intervention. This scale will be used to assess whether the intervention has an effect in reducing disease severity.
COPE-NVI (21)	The COPE-NVI is a 28-item self-report questionnaire designed to measure effective and ineffective coping strategies in response to a stressful life event (21). In this questionnaire, patients must indicate the frequency with which they use a series of coping strategies during stressful/challenging events, using a 4-point Likert scale (ranging from “I don’t usually do this = 1” to “I almost always do this = 4”). It consists of five basic scales: a) social support (referring to seeking comfort); b) avoidance strategies (denial, substance use, detachment from reality); c) positive attitude (acceptance, containment and positive reinterpretation); d) problem-focused orientation (active and strategic attitude); e) transcendent orientation (religion and lack of humour). This scale will be used to assess whether the patient develops more adaptive coping strategies as a result of the psychoeducational programme.
GAF (22)	The GAF index is a scale introduced in DSM-IV, used by mental health specialists to subjectively assess an individual’s social, occupational and psychological functioning in response to different life problems. Scores range from 100 (extremely high functioning) to 1 (severely impaired), divided into 10 levels. This scale will be used to assess the impact of psychoeducational intervention on patients’ functioning.
ISMI (23)	The ISMI scale is a 29-item questionnaire measuring self-stigma among persons with psychiatric disorders, developed in collaboration with people with mental disorders. Each item is scored from 1 (disagree) to 4 (strongly agree). This scale will be used to evaluate the fluctuations of self-stigma after the psychoeducation intervention.
MASK (24)	The Mental Health Knowledge Schedule (MAKS) is a standardised tool developed to measure the level of mental health knowledge in the general population. The scale is composed of 12 items, divided into a section on general knowledge (help seeking, recognition, support, employment, treatment, and recovery) and one dedicated to knowledge of mental illness conditions, with responses on a 5-point Likert scale. The MAKS is widely used in prevention programmes and anti-stigma campaigns as a summary indicator of mental health literacy, given its brevity and ease of administration. It will be used to assess mental health literacy after the intervention.
MOCA (25)	The Montreal Cognitive Assessment (MoCA) is a brief neuropsychological screening tool designed for the early identification of cognitive impairment and initial cognitive deficits in major neurodegenerative and cerebrovascular diseases. The test assesses multiple cognitive domains (executive functions, attention, memory, language, visuospatial skills and orientation) through a heterogeneous battery of tasks. The maximum score is 30, with a commonly adopted cut-off of 26/30, and with a correction of +1 point for subjects with ≤ 12 years of schooling. This test will be used to assess the initial cognitive level of participants in the study, trying to identify any subthreshold cognitive impairment. It will not be used as an outcome measure.

DERS, Difficulties in Emotion Regulation Scale; BPRS, Brief Psychiatric Rating Scale; CGI-S, Clinical Global Impression Scale - Severity; CGI-I, Clinical Global Impression Scale - Improvement; COPE-NVI, Coping Orientation to Problems Experienced-New Italian Version, GAF, Global Assessment of Functioning; ISMI, Internalized Stigma of Mental Illness Inventory; MAKS, Mental Health Knowledge Schedule; MOCA, Montreal Cognitive Assessment (MoCA).

During the follow-up phases, participants will be administered the following assessment tools: DERS, BPRS, Clinical Global Impression Scale - Improvement (CGI-I) (20), CGI-S, COPE-NVI, GAF, ISMI, MAKS (**Tables 2**, **3**).

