### Control intervention

3.3

The control group will receive an educational 6-session intervention, daily administered, on the following topics: a) healthy lifestyle (diet and nutrition); b) stress management; c) regulation of circadian rhythms; d) management of medication side effects (**Table 4**). The control group intervention will be administered with interacting sessions lasting 60–90 minutes provided within the group context. At the end of each session, participants will receive informative leaflets and cards summarizing the key-points addressed during the session. A dedicated training material will be provided to all staff members in order to guarantee the fidelity of administration of all sessions of the control intervention.

**Table 4 T4:** Characteristics of each module of the control intervention.

Module	Description
Healthy lifestyle (diet and nutrition) [figure not shown]	The module emphasises the importance of a varied and balanced diet for maintaining energy levels, a healthy weight and general well-being. It includes practical advice on calorie distribution throughout the day, regular consumption of fruit and vegetables, choosing whole grains and staying hydrated.
Healthy lifestyle (physical activity) [figure not shown]	The module promotes daily exercise as a means of improving sleep, mood, weight and quality of life. Simple ways to increase the amount of time spent being active and reduce sedentary behaviour are suggested.
Stress management [figure not shown]	The module helps to recognise physical, emotional and cognitive manifestations of stress and suggests immediate management exercises (breathing, muscle relaxation, music). The aim is to reduce the impact of stress in everyday life and prevent relapses.
Regulation of circadian rhythms [figure not shown]	The module explores the role of sleep in maintaining mental and physical health, linking insomnia and irregular sleep to irritability, reduced concentration and physical problems. It provides environmental, dietary and behavioural guidelines to promote a healthy sleep-wake cycle.
Management of medication side effects [figure not shown]	The module clarifies that mental disorders benefit most from a combination of pharmacological treatment and psychotherapy. It reduces prejudices about drugs, explains the main categories used and emphasises the importance of therapeutic adherence to prevent relapses.

All images were generated using AI.

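### T1 is tied to the end of courses of unequal length, so the elapsed time to T1 can often reveal the arm to raters whom section 3.2 describes as blinded

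*Protocol article*

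**What the plan says.** Section 3.2 makes an unqualified statement about the assessors: "Researchers who administer assessment tools, will be blinded to patient allocation".

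The same section fixes the first two assessments by reference to the intervention: "at T0 (baseline), at least 1 day before the start of the intervention; b) at T1 (post-intervention"). The footnote to Table 2 repeats this: "T0, baseline; T1, end of the intervention; T2, 1 month after the end of the intervention". The follow-ups T2 to T5 are also counted from completion.

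The two courses do not have the same length. Section 3.1 says of the experimental arm: "The sessions will take place each day for a total of 12 sessions for a period of around 2 weeks". Section 3.3 says of the comparator: "The control group will receive an educational 6-session intervention, daily administered".

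Three further statements bear on the point:

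- Section 3.2 lets an assessment be postponed by 2-3 days if the participant is distressed or exhausted.
- Section 3.1 lets a patient who is discharged early finish the course in person or by teleconference, with no time limit.
- Section 4 trains all professionals involved in the study in both the experimental and the control intervention.

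**The concern.** If T1 follows each patient's own last session, and one course takes about twice as long as the other, the time to T1 is close to a label for the arm. A rater does not need to be told the allocation. Knowing that one course is about twice as long, and roughly when the patient started or had the T0 assessment, is enough. Section 4 suggests that study staff will know the first of these.

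At stake are the scales that depend on the rater's judgement. Table 3 describes the BPRS as completed by the interviewer, the CGI-S and CGI-I as clinician judgements, and the GAF as a subjective assessment by a specialist. If raters can infer the arm at T1, between-arm differences on these scales are open to rater expectation, and the knowledge may carry over to T2-T5. The results would nevertheless be reported as blinded ratings.

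This is a separate matter from any drift of scores with elapsed time. The blind would be at risk even if scores did not change between day 6 and day 14.

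**Working it through.** **The plan's own figure.** The document gives no number for the security of the blind. Its one design figure, 84 patients, reproduces: the exact two-sample t calculation for d = 0.8, power 0.95 and two-sided alpha 0.05 gives 41.59, so 42 per arm (power 0.952). The present point does not alter it.

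**Inputs.**

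- Control: 6 daily sessions (section 3.3).
- Experimental: 12 daily sessions over around 2 weeks, taken as 12-14 days (section 3.1).
- T1: end of the intervention (section 3.2, Table 2 footnote). No window is given, so I assume the last session day or the day after.
- Postponement: up to 3 days (section 3.2).

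**Day of T1, with the first session on day 1.**

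Day of T1 = last session day + 0 or 1 + postponement.

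| Scenario | Control | Experimental | Gap |
|---|---|---|---|
| On schedule | 6 to 6+1 = 7 | 12 to 14+1 = 15 | 12-7 = 5 days |
| Postponed by up to 3 days | 6 to 7+3 = 10 | 12 to 15+3 = 18 | 12-10 = 2 days |

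If T0 is taken the day before the first session (day 0), the same figures are the elapsed days from T0 to T1.

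**How robust the separation is.**

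- *Weekends.* Suppose sessions may skip weekends, so that control ends on day 6-8 and experimental on day 12-16. With T1 on the last session day and a postponement of up to 3 days, the ranges are 6-11 and 12-19, a gap of 1 day. If T1 may also fall the day after, control reaches 8+1+3 = 12 and the ranges touch.
- *Stretched control courses.* A control course delayed by 5 days (12-7), or by 2 days with the full postponement (12-10), reaches the experimental range. Completion after discharge makes such delays possible.
- *T0 lag.* T0 has a minimum lead of 1 day and no maximum. If T0 precedes the start by 5 or more days longer for a control patient than for an experimental one, their T0-to-T1 intervals can coincide.

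The separation is therefore clear for patients on schedule and weakens as courses slip.

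**Which outcomes are exposed.** Table 2 lists nine instruments, and Table 3 says the MoCA is not an outcome measure, which leaves eight. Four are rater-scored: BPRS, CGI-S, CGI-I and GAF. Of these, the GAF corresponds to a secondary outcome named at the end of the Introduction (psychosocial functioning). The DERS is self-report.

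**The case against.** A reader might infer that the CGI-I forces the unblinding, since Table 3 says that "the clinician compares the patient’s overall clinical condition to the one-week period just prior to the initiation of the intervention". The document does not support this. The instruction asks for a comparison of clinical states, not for a date, and the same table entry equates the initiation of treatment with baseline, which is T0. The leak comes from the timing of T1 and would exist without the CGI-I.

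A reader might also infer that the blind has failed. That goes too far. Nothing says that raters see session or start dates, or that one rater does both T0 and T1. Masking of dates may be described in a fuller protocol, and its absence from an article is no fault. As shown above, the intervals can also overlap when courses are stretched, and the Discussion itself expects uneven attendance.

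The reach is limited too. Efficacy is judged on emotional dysregulation, measured by the self-reported DERS. The BPRS, CGI-S and CGI-I are not matched to a named secondary outcome, although the primary aim does refer to affective symptoms.

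All of this stands. What survives is narrower: the article states a blind and, in the same Methods, fixes a T1 rule that works against it. Masking session dates alone would not fully cure that, because a rater who sees the dates of the T0 and T1 visits has nearly the same information.

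**Conclusion.** The point holds as a weakness in a stated rule. Because T1 follows the end of unequal courses, the time to T1 is about 6-7 days in the control arm and 12-15 days in the experimental arm for patients on schedule. A rater who knows the start or T0 date can often infer the arm. Unblinding is likely for such patients and not certain for all.

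The conclusion rests on three assumptions: sessions run daily as sections 3.1 and 3.3 state, T1 takes place within about a day of the last session, and raters know at least one earlier date and the rough length of each course. It also rests on the Methods. The Abstract describes weekly modules, usual treatment for controls and follow-up counted from randomization; under that description the control arm has no course whose end could define T1.

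The consequence is confined to the four rater-scored scales. The size of any bias cannot be derived from the document. The point is worth correcting, but it does not threaten the DERS comparison through the rater.

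**What to change.** 1. In section 3.2, the Table 2 footnote and the Figure 1 timeline, define T1 as a fixed number of days from T0 or from randomization, the same in both arms and no earlier than the planned end of the longer course. Count T2-T5 from the same origin. State what happens to a patient still in the course on that day.
2. Have existing staff who do not rate patients book the visits, and keep session dates and attendance records from raters.
3. Optionally, have raters record a guess of the arm at T1 and report it descriptively. It should not decide whether the ratings may be called blinded, because visible improvement under an effective treatment can also drive correct guesses.

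**Cost.** This is more than a wording change, because T1 is also the first post-treatment DERS assessment, so its meaning shifts. Control patients would be assessed about a week after their last session (for example day 14 against a last session on day 6, which is 8 days), so T1 would no longer be an immediate post-course measure in that arm. Otherwise the change needs text edits, a booking rule and, if wanted, one field on the rating form. Ethics approval was still pending when the article was written, so the change is best made before recruitment starts.

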**Methods:**

Participants (aged 15-24) will attend weekly thematic modules led by psychiatrists, psychologists and trainees. The control group will receive the treatment as usual. The modules included in the intervention will address the following topics: emotions, anxiety, psychotic experiences, addictions, sleep, therapies, communication and social skills. Participants will be assessed at baseline, at the end of the intervention and at 3-, 6- and 12 months post-randomization.

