Despite the growing interest in the application of psychoeducation in adolescents and young people, the available scientific literature is still limited and fragmented. This lack of evidence makes it difficult to define solid and validated guidelines for the use of psychoeducation with adolescents, especially in more complex contexts such as acute psychiatric settings. Within this context, it has been already suggested the need to develop an age-sensitive psychoeducational intervention, able to adequately address specific adolescents’ developmental needs, by promoting a greater emotional awareness, as well as encouraging adherence to treatment pathways (10–14). Therefore, the primary aim of the present study protocol was to assess the feasibility and the efficacy of a pilot psychoeducational group intervention in a sample of adolescents and young adults with a diagnosis of emotional and/or affective disorders hospitalized within our Transition Psychiatry acute psychiatric ward, in terms of reduction of dysregulated emotional and affective symptomatology in the post-intervention and in the follow-up period. The feasibility will be assessed considering recruitment and retention rates and acceptability of the intervention, while the efficacy will be evaluated through the evaluation of emotional dysregulation pre- and post-intervention. Secondary outcomes included the evaluation of the efficacy of the intervention on the following dimensions: a) improvement of mental health literacy; b) reduction of internalized stigma; c) improvement of psychosocial functioning; d) reduction of relapses and hospitalizations during the 12-months follow-up period; e) improvement of coping strategies and expressed emotions.

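### T1 is tied to the end of each arm's own course, so the experimental arm is assessed about 6–8 days later than control, and the Abstract and Section 3.2 count follow-up from different origins

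*Protocol article*

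**What the plan says.** Section 3.2 (Measurements, assessment time-points and tools) defines the first two post-baseline visits as "b) at T1 (post-intervention); c) at T2 (follow-up at 1 months after completion of intervention" and the last as "f) at T5 (follow-up at 12 months after completion of intervention". T3 and T4 follow the same pattern at 3 and 6 months. The legend of Table 2 agrees: "T1, end of the intervention; T2, 1 month after the end of the intervention".

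The courses that set this clock are not equally long. For the experimental arm, Section 3.1 says: "The sessions will take place each day for a total of 12 sessions for a period of around 2 weeks". For the control arm, Section 3.3 says: "The control group will receive an educational 6-session intervention, daily administered". The calendar length of the control course is not stated.

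The Abstract gives a different schedule, with assessments "at baseline, at the end of the intervention and at 3-, 6- and 12 months post-randomization". It keeps T1 at the end of the intervention, moves the later visits to a randomisation clock, and has no 1-month visit.

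The Introduction ties efficacy to the visit just after treatment: "the efficacy will be evaluated through the evaluation of emotional dysregulation pre- and post-intervention".

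**The concern.** Participants are acute inpatients who all continue usual care, including medication, psychiatric visits and psychotherapy. Emotional dysregulation may well change over the first weeks of such care, whichever sessions a patient attends. If one arm is measured at about two weeks and the other at about one, the difference in DERS at T1 contains the treatment effect plus one extra week of that change. Randomisation balances the patients, but it cannot balance elapsed time that the schedule itself makes unequal. Section 5 names t-tests or rank tests and does not mention elapsed time.

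If patients improve under usual care, the bias favours the experimental arm. T1 is where it matters most, because elapsed time since the start is shortest there and the stated efficacy contrast uses that visit.

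Separately, the Abstract and Section 3.2 cannot both be followed for the 3-, 6- and 12-month visits.

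**Working it through.** **Inputs from the protocol article**
- Experimental course: 12 daily sessions, around 2 weeks (Section 3.1), taken as 12–14 days.
- Control course: 6 daily sessions (Section 3.3), taken as 6–7 days. This is an inference from the daily pace.
- Visits: T1 at the end of the intervention; T2–T5 at 1, 3, 6 and 12 months after it (Section 3.2, Table 2 legend).
- Design: 42 per arm, d = 0.8, two-sided α = 0.05, power 0.95 (Section 5).

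**Assumptions**
- The interval from randomisation to first session is the same in both arms.
- One month is 30.44 days.
- Natural change in DERS is 0.1–0.4 SD per week. The documents give no rate.

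**Step 1: the plan's own figure.** Power of a two-sample t-test, with df = 2n − 2 and noncentrality d·√(n/2):
- n = 41 gives 0.947.
- n = 42 gives noncentrality 0.8 × √21 = 3.666 and power 0.952.

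So 42 per arm (84 in total) is reproduced. The sample size is not in question here.

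**Step 2: days from start of intervention.** Day = course length + months × 30.44.

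| Visit | Experimental (12 d) | Control (6 d) | Gap | Gap as % of control time | % range over 12 v 6, 14 v 7 and 14 v 6 days |
|---|---|---|---|---|---|
| T1 | 12.0 | 6.0 | 6 d | 100% | 100–133% |
| T2 | 42.4 | 36.4 | 6 d | 16% | 16–22% |
| T3 | 103.3 | 97.3 | 6 d | 6% | 6–8% |
| T4 | 194.6 | 188.6 | 6 d | 3% | 3–4% |
| T5 | 377.2 | 371.2 | 6 d | 2% | about 2% |

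The gap is constant across visits: 6 days (12 v 6), 7 days (14 v 7) or 8 days (14 v 6). Its weight relative to elapsed time falls quickly after T1.

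**Step 3: what a one-week gap could do at T1.** Suppose there is no treatment effect. The expected standardised difference at T1 is then δ = (recovery in SD per week) × (gap in weeks). With a 7-day gap and n = 42 per arm, the noncentrality is δ × √21, df = 82 and the critical value is 1.989.

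| Assumed recovery (SD/week) | Noncentrality | P(reject), nominal 0.05 |
|---|---|---|
| 0.1 | 0.458 | 0.074 |
| 0.2 | 0.917 | 0.148 |
| 0.3 | 1.375 | 0.274 |
| 0.4 | 1.833 | 0.441 |

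**Step 4: the two clocks.** Section 3.2 and the Table 2 legend start T2–T5 at completion. The Abstract starts the 3-, 6- and 12-month visits at randomisation. On the Abstract's clock the gap disappears at T3–T5 but stays at T1, because both places leave T1 at the end of the intervention.

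The clock also affects the study calendar. Recruitment runs to month 12 and assessment to month 24 (Section 3.2). For a patient randomised at the end of month 12:
- Completion clock, experimental arm: 12 + 14/30.44 + 12 = month 24.5.
- Completion clock, control arm: 12 + 7/30.44 + 12 = month 24.2.
- Randomisation clock: month 24.0.

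**The case against.** **Assessing at the end of treatment is a recognised choice, and this is a pilot.** Both are true. But end-of-treatment timing gives a clean comparison only when the courses are about equally long, and the trial claims preliminary efficacy and is sized at 0.95 power for a DERS difference. The offset also has a simple remedy before recruitment.

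**T1 is not the only efficacy point.** This stands in part. The stated aim also covers the follow-up period, and DERS is taken at all six visits. A reader might infer that every follow-up comparison is seriously biased. The arithmetic does not support that: the offset is 16–22% of elapsed time at T2 and 2–8% at T3–T5.

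**The size of the bias is assumed.** This stands. No recovery rate appears in the documents. At 0.1 SD per week the rejection rate is 7% against a nominal 5%. The 44% needs 0.4 SD in one week of usual care, half the effect the trial is sized for. The range shows sensitivity; it does not estimate bias in this trial.

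**Patients who stop attending.** A reader might infer that they have no assessment date and that the available-data analysis becomes a comparison of completers. The documents do not establish this. Section 3.2 says that all patients will be assessed, and the end of the intervention can mean the scheduled end of the course, which exists for everyone. Nothing limits assessment to completers. Rules for early stoppers may also stand in the full protocol. A one-line clarification is worth adding, but its absence is not an error.

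**A common date creates its own asymmetry.** This also stands. Control patients would be assessed about a week after their last session, and a day fixed too early could precede the last experimental session. It bears on which common day to choose.

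**Conclusion.** The point holds for T1. As written, the experimental arm reaches T1 about 6–8 days later than control, at roughly twice the elapsed time, and the pre/post efficacy contrast on DERS confounds this with treatment. The same offset is moderate at T2 and small from T3 on.

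The timing gap rests on two things not stated outright: that 6 daily sessions take about a week, and that both arms start equally soon after randomisation. The inflation of the false-positive rate, from 5% to between 7% and 44%, depends wholly on the assumed recovery of 0.1–0.4 SD per week.

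The conflict between the Abstract and Section 3.2 over the origin of the 3-, 6- and 12-month visits needs no assumption and must be reconciled. The sample size of 84 is unaffected.

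**What to change.** 1. Time every post-baseline visit from randomisation, identically in both arms and with the same windows.
2. Set T1 on one common day at or just after the scheduled end of the longer course (about 2 weeks of sessions), counted from randomisation and allowing for the interval before the first session. Day 14 exactly could fall before the last experimental session.
3. Set T2–T5 at common times from randomisation. A 1-month visit on that clock falls only about 2 weeks after the experimental course ends, so the sponsor should decide whether that is the interval wanted at T2. A 12-month visit on that clock falls by month 24.0, within the stated assessment period.
4. State that every randomised patient is assessed on these dates regardless of sessions attended.
5. Align Section 3.2, the Table 2 legend and the Abstract, including the 1-month visit that the Abstract omits.

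**Cost.** Protocol wording, no extra visits and no change to N. The between-arm gap in scheduled timing becomes zero at every visit. The downside is that control T1 moves to about a week after the control sessions end. Given the ward's short stays, it may more often fall after discharge, with some risk of extra missing data in that arm. The protocol should name this and plan to obtain those assessments.
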